### 6.4. Test and Re-Test Analysis and Sample Size

Initially, the examiners were instructed by an experienced pediatric orthopedic consultant in the full examination program, and a pilot evaluation with three formal tests of five representative, typically developed children with the full evaluation program was performed by all examiners at least a week apart as an initial evaluation of the intra- and inter-variability [40,41]. The results were performed to evaluate each parameter to be evaluated with a goniometer or as a binary parameter as well as how these tests should be performed. The examiners were then re-instructed in the examination program. A test and re-test analysis was carried out in the spring of 2023 with a subset of 50 children. This sample size is often recommended for test–retest studies [42]. Multiple examiners independently assessed these children at two different time points less than 4 weeks apart. To quantify the reliability of our assessments, we will calculate reliability coefficients using intra-class correlations (ICC 3.1) [43]. Additionally, we will express absolute measurement errors using limits of agreement [44]. To enhance the clinical relevance of our study, we will engage three chief orthopedic surgeons to provide insights into acceptable measurement errors in our context. Each surgeon will independently assess what they deem as clinically acceptable thresholds for measurement errors. Should there be any discrepancies in their assessments, a joint meeting will be organized to discuss and reach a consensus. The agreed-upon acceptable thresholds will guide our interpretation of the limits of the agreement.

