### 5.2. Clinical Examinations

The clinical examination in this study is based on the prevalence of pathologies in children to obtain data on the normal material of these children. This entails the examination and registration of the following: -Mapping the foot anatomy and pathologies of warts, foot deformities, ingrown toenails, callosities, hallux valgus, metatarsus varus, and the ROM of the subtalar joint and midfoot, hindfoot valgus, navicular height, static foot pressure mapping, and foot type (square, Roman, or Greek) [26].-Mapping the anthropometric data on children’s height and weight, hip range of motion (ROM) (flexion, internal and external ROM [27], the ROM of knee flexion, and the extension ROM of the ankle joint on a flexed and extended knee [27], as well as the femoral anteversion and torsion of the tibia (foot–thigh ankle)). This is evaluated when the child is either standing, prone, or supine in a standardized manner and using a goniometer (see Supplementary).

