### 6.3. Statistical Analysis and Randomization 

Three clusters of equally divided children from the 1st grade, 5th grade, and 9th grade will be evaluated. This was chosen to embrace the spectrum of chronological (with different developmental stages) ages in Danish primary schools. The total planned number of included children is a thousand children. The sample size was chosen based on a balance between the desired statistical robustness and the practical constraints of this study. These constraints include available resources, such as funding, staffing, and logistics. This sample size is in line with or larger than similar large-scale, observational studies in pediatric populations [36,37,38], where specific power calculations can be more complex due to the multitude of variables and outcomes being explored. We acknowledge this as a limitation but also believe that the chosen sample size is sufficient to provide meaningful and robust data for the objectives of our study. The schools will be chosen randomly with the measure of crow fly distance and the number of children in the schools (>1000). A school’s socioeconomic status will be registered based on the ‘Socioøkonomisk reference for grundskolekarakterer 2018/2019′ [36]. The normality of the data will be assessed graphically using quantile–quantile and density plots. 

Based on their distribution, variables will be described using either means and standard deviations (for normally distributed data) or medians and interquartile ranges (for non-normally distributed data). Appropriate hypothesis tests will be conducted based on the distribution of the data. These include Student’s t-test and Wilcoxon’s rank-sum test for continuous data. For categorical data, chi-square tests and Fisher’s exact test will be used as appropriate. *p*-values of ≤ 0.05 will be considered statistically significant. Simple bivariate analyses will be conducted to establish initial associations between potential predictor variables and relevant outcome variables. To investigate the associations between pain and lower extremity kinematic and alignment variables, we will use multilevel multivariable logistic regression models, stratified by grade (1st, 5th, and 9th). Examiner ID will be included as a random factor in the models. The statistical analysis will be performed using the newest available version of R [39].

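### ICC(3,1) is named for reliability across several examiners, but it drops systematic examiner differences, so between-examiner reliability can be overstated

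*Protocol article*

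**What the plan says.** The reliability sub-study is in Section 6.4: "A test and re-test analysis was carried out in the spring of 2023 with a subset of 50 children". Its design is given in one sentence: "Multiple examiners independently assessed these children at two different time points less than 4 weeks apart". The number of examiners, and whether each of them saw every child on both occasions, is not stated. The only coefficient named is the intra-class correlation: "To quantify the reliability of our assessments, we will calculate reliability coefficients using intra-class correlations (ICC 3.1". No ICC target or cut-off is set.

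Section 6.4 adds limits of agreement for absolute error. Three senior orthopedic surgeons are to agree on tolerable measurement errors, and those tolerances are tied to the limits of agreement, not to the ICC. The text does not say whether the limits compare two examiners or two sessions of one examiner.

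On the main analysis, Section 6.3 says of the pain models: "Examiner ID will be included as a random factor in the models". Section 6.1 has the examining podiatrists record each child's data, and Section 2.1.2 lists six podiatrists in the team. The first purpose in the Introduction is reference material on the foot, rotational status and joint motion. Section 6.3 describes variables by means and SDs or by medians and interquartile ranges, with no stated examiner adjustment.

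**The concern.** ICC(3,1) asks whether examiners rank children alike after each examiner's own average has been removed. That suits a setting in which an offset does no harm, for example when one examiner measures everyone. Here several examiners contribute readings to one pool. If one of them reads a joint angle several degrees higher than the others, that offset widens the reference distribution and can shift values for the children that examiner saw. A coefficient that cannot register the offset may then be cited as evidence that the readings are interchangeable.

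Section 6.3 shows that examiner variation is expected, since examiner enters the pain models as a random factor. That term may absorb part of an offset in those models, but it does nothing for the descriptive reference values. Section 7 presents the test–retest study as the check on how far the results generalize, so the choice of coefficient matters.

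**Working it through.** **Inputs from the documents.** 50 children, several examiners, two sessions and ICC 3.1 (Section 6.4); six podiatrists in the team (Section 2.1.2). The plan gives no ICC value, variance component or precision target, so there is no figure of its own to reproduce. The sample size rests on a citation: "This sample size is often recommended for test–retest studies".

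**Reading of the notation.** ICC 3.1 is taken as ICC(3,1): two-way mixed model, single rating, consistency.

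**Assumed inputs, for illustration only.** A goniometer angle with child SD 8 degrees (variance 64), residual SD 4 degrees (variance 16) and examiner SD s = 0, 2, 4 or 6 degrees.

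**Formulas.**
- ICC(3,1) = V_child / (V_child + V_residual)
- ICC(2,1) = V_child / (V_child + V_examiner + V_residual)
- Half-width of the limits of agreement between two randomly chosen examiners = 1.96 × √(2 × (V_residual + V_examiner))

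**Results.**

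| Examiner SD | ICC(3,1) | ICC(2,1) | Between-examiner limits |
|---|---|---|---|
| 0 | 64/80 = 0.80 | 64/80 = 0.80 | 1.96 × √32 = ±11.1 |
| 2 | 64/80 = 0.80 | 64/84 = 0.76 | 1.96 × √40 = ±12.4 |
| 4 | 64/80 = 0.80 | 64/96 = 0.67 | 1.96 × √64 = ±15.7 |
| 6 | 64/80 = 0.80 | 64/116 = 0.55 | 1.96 × √104 = ±20.0 |

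ICC(3,1) stays the same in every row. The gap is 0 in the first row and 0.80 − 0.55 = 0.25 in the last.

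**Check at the study's size.** The estimators were simulated with 50 children and six examiners (an assumption), child variance 1 and residual variance 0.25, which is the same ratio as 64 to 16. Over 2,000 runs the mean ICC(3,1) and ICC(2,1) were 0.795 and 0.795 at examiner variance 0, 0.794 and 0.665 at 0.25, and 0.793 and 0.582 at 0.50.

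**What the limits of agreement would show.** Take two examiners who differ by a constant 5 degrees.
- Between examiners: the limits are 5 ± 11.1, or −6.1 to 16.1 degrees, so the offset is visible. The examiner variance is 5²/2 = 12.5, and ICC(2,1) = 64/92.5 = 0.69 against ICC(3,1) = 0.80.
- Within examiner across sessions: the offset is in both readings and cancels. With the same residual variance the limits return to ±11.1, and neither statistic shows the difference.

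**Binary and nominal items (secondary).** In large simulated samples with two examiners, ICC(3,1) and kappa were 0.556 and 0.556 when both scored 20% positive, 0.542 and 0.528 at 20% and 30%, and 0.403 and 0.356 at 10% and 30%. For a three-category nominal item with confusion between two categories, kappa was 0.66, while ICC(3,1) was 0.85 or 0.16 depending only on the order of the codes.

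**The case against.** The strongest reply is that the ICC is not the plan's criterion. Section 6.4 sets no ICC cut-off and attaches its agreed tolerances to the limits of agreement, which are in degrees and would show an offset if taken between examiners. This stands: a reader might infer that ICC(3,1) alone will pass or fail parameters, and the text does not support that. What remains open is which limits are meant, and within-examiner limits would not help.

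Second, the examiners were instructed, took part in a pilot of three tests on five children and were re-instructed before the 50-child study. Systematic differences may therefore be small. This also stands. A reader might infer that reliability will be overstated, but the documents give no examiner variance, and with none the two coefficients agree. ICC(3,1), however, cannot tell which case applies.

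Third, a random examiner term in a pain model and a fixed-examiner reliability coefficient answer different questions, and fixed examiners are defensible if the reliability examiners are also the study's examiners. It would go too far to call Sections 6.3 and 6.4 a contradiction. But even with fixed examiners, pooled readings call for absolute agreement rather than consistency.

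Fourth, the article does not say that the ICC will be applied to categorical items. It mentions "each parameter to be evaluated with a goniometer or as a binary parameter" when describing the pilot and lists "foot type (square, Roman, or Greek" in Section 5.2. A condensed article may leave kappa to the full plan. For binary items the ICC is close to kappa, and for nominal items the error can go either way, so no general overstatement follows. This part is secondary.

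**Conclusion.** The point holds in a conditional form. The coefficient named for a multi-examiner study is blind to systematic examiner differences, and these count as error in the pooled reference values. Between-examiner reliability can therefore be overstated. On the assumed variances the overstatement is 0, 0.04, 0.13 or 0.25 for examiner SDs of 0, 2, 4 or 6 degrees; the true size cannot be known from the documents.

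The conclusion rests on the usual meaning of ICC(3,1), and on each child's value in the main study coming from one examiner. The latter is inferred from podiatrists recording the data and from examiner ID being a model term. The planned limits of agreement are a partial safeguard whose form is not specified. The severity is moderate: design, sampling and outcomes are unaffected.

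**What to change.** In Section 6.4, separate the two questions.

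- **Between examiners, continuous items:** report ICC(2,1) (two-way random, absolute agreement) with a 95% confidence interval. Compute the limits of agreement between examiners so that examiner differences are included, and apply the surgeons' tolerances to those limits.
- **Same examiner, two sessions:** ICC(3,1) may be kept here at most, with limits labelled as within-examiner.
- **Binary and nominal items (secondary):** report kappa with percent agreement.
- **Design:** state how many examiners took part and which children each saw at each session.

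The cost is a change of analysis wording, with no new measurements if examiners were sufficiently crossed with children. That is not stated and should be confirmed first, because it determines whether examiner variance can be estimated. Reported reliability may come out somewhat lower, and with few examiners the confidence interval for ICC(2,1) may be wide.

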## 7. Expected Results

The focus on children’s health is essential for children, caregivers, and healthcare professionals such as school nurses, doctors, and podiatrists [1,2]. The lower extremities and feet of typically developed children are an area that causes pain [5]. Specific sports activities seem to impact the health of Danish children’s diseases of the lower extremities and feet, leading to pain [45,46], which, subsequently, will lead to activity restrictions and, if causing musculoskeletal overuse injury, healthcare service needs. To improve the care of children’s feet, a project for the evaluation and screening of children’s feet and lower extremities in Danish primary schools was initiated in the fall of 2022. The interdisciplinary project between physicians, researchers, and podiatrists will examine the extent of lower extremity and foot diseases in children by evaluating children in the first, fifth, and ninth grades of primary school. The project aims to identify areas of improvement in the care of children’s lower extremities and feet with the tenets of creating a prospective database using online submitted PROMs for further follow-up during adolescence and into adulthood and of providing recommendations for preventive actions for healthcare professionals. The study design is a cross-sectional examination of a thousand children, analyzing their clinical status, pain levels, sports activities, foot dimensions and pressures, and footwear. This study will measure foot dimensions using commercial 3D scanning techniques and assess the fitting of footwear. This project will help provide insights into the health of children’s feet and potential mismatches between foot size and footwear that could lead to deteriorating foot health. This project’s findings aim at developing recommendations concerning anthropometric parameters that might be preconditions for pain, the three-dimensional foot dimensions and foot pressure mapping, and the intensity and type of sports activity as a potential preventive measure from the perspective of socioeconomic inequality on a group level and activity status with the tenet of minimizing unintended consequences, such as performing specific high-intensity sports if preconditioned for pain, for Danish children’s foot health. However, as eluded earlier, the need for elucidating these issues is national, but these issues relate to children worldwide, and this project could be expanded internationally since the clinical and instrumental evaluations, commonplace clinical examinations, and PROMs are translated into several languages; thus, this project would be ‘translational across countries’.

This study is expected to provide information on misalignments and malpositions, deformities, gait patterns, footwear, and skin and foot hygiene in the lower extremities and feet of Danish children, and this will be examined from the perspective of detecting and clarifying the role of sports activities and socioeconomic inequalities on a group level. When analyzing and interpreting data in this study and drawing conclusions thereof, the generalizability will rely upon the specificity of the evaluation methods and sample size. In this study, we will perform a test–retest study and subsequent power analyses to evaluate this. We foresee that we will identify subgroups with specifically located pain [45,46]; thus, we will have to be aware of generalizing small subgroups to the general pediatric population. Therefore, unusual, single, or unexpected results must be carefully considered concerning the profile of other results and their plausibility. Nonetheless, the results obtained in this study may have an impact on public health concerning physical (sports) activity, the mapping of podiatric diseases, and anthropometric parameters in children [47,48].

In conclusion, this study will focus on children’s lower extremities and feet to evaluate the relationship between pain status and physical (sports) activity and the mapping of podiatric diseases. Moreover, this will be examined in the context of socioeconomic status on a group level, foot health, and quality of life. This project evaluating children’s feet and lower extremities in Danish primary schools is a step toward identifying areas of improvement in the care of children’s feet and providing recommendations for parents and healthcare professionals. Overall, this study can potentially have an impact on public health concerning physical activity status and anthropometric parameters in children, which can be the first step in improving children’s foot health and quality of life [48,49].

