### 6.1. Availability of Data and Materials

The data in this study will be registered and reported in a REDCap database following the GDPR rules of the Danish data protection agency and will be stored for 5 years after this study has ended. The data of each subject will be filled out by the examining podiatrists assisted by the TAP employee directly on paper, which afterward, will be transferred to the REDCAP database by TAP employees with secure internet access to register/record the data of this study directly in the REDCAP database as well as for any of the apparatus used in this study. General information about the children will be collected from the primary caregiver of each patient using the methodology via Aula and REDCap as described in Section 2.1.

All relevant information collected during this study will be passed on to the participating doctors for evaluation, if necessary. Information regarding the patients will be passed on directly to the participating doctors, if necessary, by using “…@regionh.dk” emails or directly, using the REDCAP database to ensure the protection of the data. All transfers of data will comply with and have been approved according to the current GPDR rules. 

All data about the patients will appear pseudo-anonymized using the patients’ ID numbers. Information will be kept on a logged and secure drive in the RegionH intranet system. Information from medical records will not be retrieved, but data to provide information about this study to the parents and inquire about informed consent will be required to contact them by letter, as described in Section 2.1. This information includes name, age, CPR number, gender, address, and email. All information regarding the patients will be protected according to “Lov om behandling af personoplysninger og Sundhedsloven, afsnit 3 ver. patienters retsstilling”. Information regarding this study, and, thus, the patients, will also be passed on to governmental agencies (health authorities and the Danish Data Protection Agency if an inspection of this study is requested). Data will not be transferred to other countries. The dataset for this study has been generated and is under preliminary analyses and is thus not currently publicly available. For further interest, inquiries about the data can be sent to the corresponding author.

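### Power analyses after data collection are named for judging generalizability and sample size; clustered confidence intervals, participation rate and school mix would serve better

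*Protocol article*

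**What the plan says.** Section 7 (Expected Results) says that "the generalizability will rely upon the specificity of the evaluation methods and sample size". The next sentence names the means of checking, a test–retest "study and subsequent power analyses to evaluate this". The same paragraph warns against extending findings in small pain subgroups to children in general.

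Four other places bear on this:

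- Section 6.3 fixes the size: "The total planned number of included children is a thousand children". It gives the basis as follows: "The sample size was chosen based on a balance between the desired statistical robustness and the practical constraints of this study". No target power, effect size or precision is stated. The section acknowledges this as a limitation, yet holds that "the chosen sample size is sufficient to provide meaningful and robust data for the objectives of our study".
- Section 6.1, on the state of the data: "The dataset for this study has been generated and is under preliminary analyses".
- Section 6.4, on reliability: "A test and re-test analysis was carried out in the spring of 2023 with a subset of 50 children". Intraclass correlations, limits of agreement and agreed error thresholds are to follow.
- Section 6.3 plans descriptive summaries, hypothesis tests at 0.05, and multilevel logistic models for pain by grade, with examiner as the random factor.

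**The concern.** The article commits itself to a tool for deciding how far its conclusions reach. Power is the probability of rejecting a null hypothesis under an assumed effect. Before a study it helps to set the sample size. Once the data exist it can no longer do that, and the remaining question is how precisely each quantity has been estimated, which an interval answers directly.

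Who the results apply to is a different question. It turns on how the 20 schools in two regions were chosen and on which families consented. Section 3.1 says inclusion continues until a thousand children are in. The sample size, and any power derived from it, would therefore be the same whether most or few of the invited families took part.

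The article intends to use the results for recommendations on footwear and sport. A power figure could make a wide, inconclusive subgroup estimate look settled, or a precise null look merely underpowered.

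**Working it through.** **1. Can the plan's own figure be reproduced?** No. The thousand children come with no power, effect size, event rate or precision target, so there is no calculation to check.

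**2. When would the power analyses take place?** Grammatically, they follow the test–retest study, which Section 6.4 dates to spring 2023. Section 6.1 reports the dataset as generated. That they come after data collection is an inference from these two sections, and a well-supported one.

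**3. What would power add?** The article does not say which effect would be used, so both cases are shown, at two-sided 0.05 (sidedness is assumed).

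*(a) At the observed effect.* Observed power = Φ(z − 1.96) + Φ(−z − 1.96), where z is the normal quantile for the two-sided p-value.

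| p | Observed power |
|---|---|
| 0.01 | 73% |
| 0.05 | 50% |
| 0.20 | 25% |

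This is a fixed function of p. It is also silent on precision. Take two equal groups with rates near 50% and a result at p = 0.05:

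- Total n = 100: SE = √(0.25 × 2/50) = 0.100. The difference is 1.96 × 0.100 = 19.6 points, and the interval runs from 0 to 39 points.
- Total n = 1000: SE = √(0.25 × 2/500) = 0.0316. The difference is 6.2 points, and the interval runs from 0 to 12 points.

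Observed power is 50% in both.

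*(b) At an effect fixed in advance.* Here power does not restate p. For assumed rates of 20% and 30% in equal groups, power = Φ[(0.10 − 1.96 × SE₀)/SE₁], with SE₀ = √(2 × 0.25 × 0.75/n) and SE₁ = √((0.16 + 0.21)/n), n per group.

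- 500 per group: (0.10 − 1.96 × 0.0274)/0.0272 = 1.70, power 0.96.
- 166.5 per group (one grade): (0.10 − 1.96 × 0.0475)/0.0471 = 0.15, power 0.56.

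This bears indirectly on sample size, but it says nothing about the precision of a prevalence or reference value, or about who took part.

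**4. What do intervals show instead?** Inputs: 1000 children in three equal grade groups, so about 333 per grade (Section 6.3), and 20 schools (Section 2.1.2). Assumed: 20% prevalence, school intraclass correlation (ICC) 0 to 0.05, equal school sizes.

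Half-width = 1.96 × √(0.2 × 0.8/n × DE), with DE = 1 + (n/20 − 1) × ICC.

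| n | ICC 0 | ICC 0.02 | ICC 0.05 |
|---|---|---|---|
| 333 (one grade) | DE 1.00, 4.3 points | DE 1.31, 4.9 points | DE 1.78, 5.7 points |
| 1000 (all) | DE 1.00, 2.5 points | DE 1.98, 3.5 points | DE 3.45, 4.6 points |

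For prevalences from 10% to 50%, the per-grade half-width runs from 3.2 to 5.4 points unclustered and from 4.3 to 7.2 points at ICC 0.05. The 5% dropout in Section 3.1 leaves about 317 per grade and changes the first row only to 4.4, 5.0 and 5.8 points.

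**The case against.** The strongest defence reads the two sentences in parallel: test–retest checks the methods, power checks the sample size, and neither is offered as a test of external validity. Power computed after a reliability study, at a fixed effect and using the measured error, would be a reasonable exercise. This reading is plausible, and it rules out treating the sentence as a plan for observed-effect power. Even so, interval width describes what the achieved sample supports more directly than power does, and the passage still bases generalizability on measurement and sample size.

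A reader might infer more than the text supports in three ways:

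- *That the power analyses will merely restate the p-values.* This holds only for power at the observed effect, which the article nowhere specifies.
- *That power is the whole evaluation.* It is not. The test–retest study, with its intraclass correlations and limits of agreement, is the other half and is appropriate for reliability.
- *That Section 6.3 is confined to p-values and so excludes confidence intervals.* It also plans descriptive summaries and regression models, and an article may leave interval reporting to the full plan. That silence is no defect.

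It is also fair to say that the paragraph already cautions about small subgroups, that the missing power calculation is acknowledged, and that the half-widths above show what the sample can deliver, not harm done by a power analysis.

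**Conclusion.** The point holds in a limited form. The article names power analyses as part of how generalizability and sample size will be evaluated. Done once the data exist, they cannot show to whom the results apply, and they are less informative than interval widths about what a thousand children support. The test–retest study does not fill that gap, because reliability is a separate property.

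The impact is modest. The sentence stands in Expected Results, and no planned test or model depends on it. The timing rests on Section 6.1, and the half-widths rest on the assumed prevalence and school ICC. The conclusion about generalizability rests on neither the assumed figures nor the choice of effect size for the power analyses.

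**What to change.** Keep the test–retest study. Replace the reference to later power analyses with wording to this effect:

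> Prevalences, reference values and odds ratios will be reported with 95% confidence intervals, overall, by grade and in pain subgroups, allowing for clustering of children within schools. Precision will be judged from the widths of these intervals. Generalizability will be judged from the participation rate and the mix of participating schools.

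The cost is a small extra analysis as well as the rewording. Section 6.3 names only examiner as a random factor, and its multilevel models cover pain associations only. A school random effect or cluster-robust standard errors must be added to those models, and clustered intervals must be produced separately for prevalences and reference values. The intervals will be somewhat wider than unclustered ones, as the table shows. The participation rate needs the number of children invited at each school.
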